### Research ethics

All the participating sites are required to pass the review by the ethics committee of the center and obtain a certificate before they can conduct research. Patients or authorized family members of patients are required to sign informed consent forms prior to patient randomization. An independent Data and Safety Monitoring Board (DSMB) will be established to periodically review the accumulated safety and efficacy data. The trial may be terminated early on the basis of DSMB recommendations for compelling evidence of superiority, futility, or safety concerns.

### Definitions and reporting of adverse events

#### Definitions of adverse events

Adverse events (AEs) were defined as untoward medical events that occur after participants have been enrolled but are not necessarily relevant to this study. The severity of AEs will be determined by the following criteria: mild, did not affect daily activities; moderate, affected daily activities; and severe, lost the ability to perform daily activities. Serious adverse events (SAEs) were defined as those requiring hospitalization for ≥2 months or resulting in death due to surgical complications during the clinical study.

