### Study endpoints

Main endpoint indicator: The 3-year DFS rate. Secondary endpoint measures include the following: lymph node yield; operative time; postoperative (30-day) morbidity (anastomotic leakage, incision site infection, postoperative abdominal hemorrhage, gastrointestinal bleeding, intra-abdominal infection, pulmonary infection, urinary system infection, chyle leakage, postoperative intestinal obstruction, cardiovascular event, cerebrovascular event, thrombotic disease, urination disorder, other) and mortality.

Adverse reaction indicators: The occurrence of postoperative complications and treatment measures will be recorded in detail. All adverse events will be recorded and those resulting in hospital admission, prolonged hospital stay, additional surgical or medical treatment, or death will be reported.

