
The blinding of surgeons and patients is not feasible. However, this approach may introduce bias in postoperative management (e.g. timing of drain removal, discharge criteria) and the assessment of subjective symptoms.

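### The only severity scale the article fixes grades complications by effect on daily activities, which ranks early postoperative events poorly and has no level for reintervention or threat to life

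*Protocol article*

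**What the plan says.** Three places in the protocol article bear on this.

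- **Definitions of adverse events.** Adverse events are "untoward medical events that occur after participants have been enrolled but are not necessarily relevant to this study". Their severity is set on three levels: "mild, did not affect daily activities; moderate, affected daily activities; and severe, lost the ability to perform daily activities". Serious adverse events are those "requiring hospitalization for ≥2 months or resulting in death due to surgical complications" during the study.
- **Study endpoints.** The secondary endpoints include "postoperative (30-day) morbidity (anastomotic leakage, incision site infection, postoperative abdominal hemorrhage, gastrointestinal bleeding" and further named complications, ending with "cardiovascular event, cerebrovascular event, thrombotic disease, urination disorder, other) and mortality". No severity grade is attached to this list. The same section states: "The occurrence of postoperative complications and treatment measures will be recorded in detail". It adds that, among adverse events, "those resulting in hospital admission, prolonged hospital stay, additional surgical or medical treatment, or death will be reported".
- **Discussion.** On the lack of blinding of surgeons and patients, the article concedes that "this approach may introduce bias in postoperative management (e.g. timing of drain removal, discharge criteria) and the assessment of subjective symptoms".

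**The concern.** Surgical complications are a named short-term outcome in the Abstract and the Objectives. The high-ligation arm adds cephalad mobilisation of the vein and dissection of the nodes at its root (Major surgical steps). Whether that extra dissection adds major surgical harm is therefore a natural secondary question, and it needs a rule that separates major from minor complications.

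The one severity rule in the article is poorly suited to that. Shortly after a rectal resection, daily activities are limited by the operation, so a rater has to guess how much of the limitation comes from the complication. The top level is loss of activity, so a conservatively managed ileus and a leak that needs reoperation can receive the same grade. The rating is a matter of judgement, and the Blinding section names blinded assessors only for imaging recurrence and for lymph nodes (besides the data analysts), not for complications.

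At stake is how clearly the trial can report the harm side of its comparison. A difference in major complications could go unremarked if overall occurrence is similar in the two arms. Choosing a severity rule only after the data are in would not have the standing of a prespecified one.

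**Working it through.** The article gives no figure on this point to reproduce. The check is a reading of its rules side by side.

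1. **Does the scale cover surgical complications?** Yes. Any untoward medical event after enrolment is an adverse event, so each complication listed under Study endpoints falls under the scale.

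2. **Is there another severity scale?** No. Study endpoints, Safety evaluation and analysis, Statistical analysis, Definitions of adverse events and SAE reporting contain no surgical complication classification.

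3. **Does the seriousness rule fill the gap?** No. It has two routes: a stay of two months or more, or death due to surgical complications. A reoperated or life-threatening complication in a patient who survives and leaves hospital within two months meets neither. Major non-fatal morbidity is therefore marked out neither by severity nor by seriousness.

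4. **Is the morbidity endpoint compared on this scale?** The article does not say so. As written, the endpoint is the occurrence of named complications, with mortality beside it. The Statistical analysis section has a chi-square test for counts and a Wilcoxon rank-sum test for graded data, but ties neither to complication severity.

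5. **Could a better grade be derived?** Yes. Treatment measures are recorded, and events leading to admission, prolonged stay, additional treatment or death are reported. The raw material exists; the article states no rule for using it.

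**Illustration only.** The rates below are assumptions, not taken from the documents. The 758 per group is the planned enrolment from Number of research cases. Suppose 20% of each arm has any complication, so the occurrence comparison shows a difference of 0. Suppose further that 8% against 4% need reintervention.

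- Patients: 0.08 × 758 ≈ 61 and 0.04 × 758 ≈ 30.
- Pooled proportion: (0.08 + 0.04)/2 = 0.06.
- Standard error: √(2 × 0.06 × 0.94/758) = 0.0122.
- z = 0.04/0.0122 ≈ 3.3.

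Halving the assumed gap (6% against 4%) gives a pooled proportion of 0.05, a standard error of √(2 × 0.05 × 0.95/758) = 0.0112 and z = 0.02/0.0112 ≈ 1.8. With no gap, z = 0. The example shows only that equal overall occurrence can coexist with a detectable difference in major events. It does not estimate any loss in this trial.

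**The case against.** The strongest reply is that the scale and the endpoint are separate. Morbidity is a list of named events, so a leak and a urinary infection are different entries whatever grade each receives. Deaths are counted separately, and reinterventions can be read from the recorded treatments. This stands. A reader might infer that the morbidity comparison cannot tell trivial from life-threatening events. The documents do not support that: they nowhere say morbidity is compared on the daily-activities scale, and they collect what is needed to make the distinction. For the same reason, the reinterventions in the illustration would be recoverable from the planned data.

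A second reply is that a complication grading system is the kind of detail an article leaves to the full protocol or analysis plan. This stands in part. The absence of a treatment-based grade from the article alone would be no finding, and a fuller document may contain one. But the daily-activities scale is a stated choice, and it is that choice which fits badly.

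A third reply is that the scale grades the effect of the event, not the background of recovery, so an infection that adds no limitation would be mild. That is a fair reading, and it means one cannot claim that the scale is unable to rank events at all. It leaves the rater to separate two sources of restriction by judgement, and it does not create a level for reintervention or threat to life.

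A fourth reply is that the admission in the Discussion covers postoperative management as well as subjective symptoms, so a grade based on treatment is also exposed to unblinded decisions. This is right, and it is a limit of the remedy. Even so, whether a reoperation took place is a recorded fact, whereas interference with daily activities is an impression.

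**Conclusion.** The concern holds in a limited form. The article fixes one severity scale, and it suits early complications of rectal resection poorly: it is subjective, it is confounded with ordinary recovery, and it stops short of reintervention and threat to life. The serious adverse event definition leaves the same gap. No severity-based comparison of major 30-day morbidity is prespecified in the article, although the data for one are to be recorded.

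The consequence is confined to the clarity of a secondary safety comparison. The primary endpoint, the sample size and the reported occurrence of each named complication and of death are unaffected. It is worth correcting because the correction is cheap. The conclusion rests on the article alone and on the assumption that no document not shown already sets a treatment-based grade.

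**What to change.** In Definitions of adverse events, replace the daily-activities scale for postoperative complications with the Clavien-Dindo classification, derived from the treatment measures already recorded under Study endpoints. The existing scale can remain for other adverse events.

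In Study endpoints, keep the listed complications and mortality, and prespecify two per-patient 30-day comparisons: any complication, and highest grade III or above (reintervention, organ failure or death). Both are yes/no outcomes that the chi-square test already named can handle. If a document not shown already sets such a grade, the article need only refer to it.

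The cost is coding on the case report form and a briefing for research staff, with no added visits or procedures. The remaining weakness is that the grade follows treatment decisions made by teams who know the allocation; the report should say so.

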### Data management

#### Data entry

Data-management personnel: Research assistants and follow-up personnel of each subcenter. Data managers should upload and review research data in a timely manner to ensure data accuracy and their main responsibilities are as follows:

Recording: synchronous data entry is performed.Auditing of data: each item in the database is checked and found to be inconsistent, and the original data are checked and corrected sequentially.During the trial, the informed consent of the subjects and the screening of inclusion should be checked regularly.Confirm that all case report forms are completed correctly and are consistent with the original data.Based on the internet database, real-time monitoring and online quality control are conducted. Once data problems are identified, telephone inquiries are conducted in time to modify the data.Withdrawals and loss to follow-up of verified participants are described in the case report form.It is confirmed that all adverse events have been documented and that serious adverse events have been reported and documented.

Statistician: [name]. Statisticians are responsible for data collection, collation, and analysis. The details are as follows:

Locking of the database: after the research is completed, the database will be locked and the locked data are not allowed to change in principle; if changes are required due to special circumstances, the data manager must apply in writing to the person in charge of the study to explain the reason for the application for unlocking, and the person in charge of the study and the statistician shall negotiate to determine whether to agree to the unlocking.Data analysis: the database is analysed according to a statistical plan.

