#### Safety evaluation and analysis

Safety analysis (SS) population: All subjects who have had at least one safety assessment after randomization should be included. The security analysis should use the security dataset of the analysis population. Safety datasets: Ineffective cases are considered to be the worst-case scenario, such as the evaluation of liver function, which is considered to be the worst, unlike the ITT analysis, which presents the most recent results and may be improved.

It is based mainly on the occurrence of adverse events and serious adverse events, and the population data are analysed with safety analysis.

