#### SAE reporting

When an SAE occurs, reasonable medical measures must be taken immediately. The physician or research assistant who has confirmed the SAE should report to the research director of the participating institution; the person in charge of the research unit or the acting person in charge of the research unit shall report the SAE to the person in charge of the study within 24 h of the discovery of the SAE, the person in charge of the study shall report the SAE to the ethics committee of the unit, and the ethics committee of the unit shall fully assess the urgency, importance, and impact of the SAE. After evaluation and discussion, the study may be suspended if necessary.

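### The serious adverse event definition (a stay of at least 2 months, or death from surgical complications) keeps survived life-threatening complications with shorter stays, and deaths from other causes, out of the 24-hour reporting route

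*Protocol article*

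**What the plan says.** Four parts of the protocol article bear on this point.

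- **Definitions of adverse events.** Adverse events are graded mild, moderate or severe by their effect on daily life; the top grade is "severe, lost the ability to perform daily activities". Seriousness is defined separately, by two criteria only: an event "requiring hospitalization for ≥2 months or resulting in death due to surgical complications".
- **SAE reporting.** The person in charge at the site must "report the SAE to the person in charge of the study within 24 h of the discovery of the SAE". The study lead then informs the ethics committee, which assesses the event, and the study may be suspended. All of this starts from an SAE.
- **Study endpoints.** All adverse events are to be recorded, and "those resulting in hospital admission, prolonged hospital stay, additional surgical or medical treatment, or death will be reported". No deadline or recipient is named, and the text neither calls these events SAEs nor refers to the 24-hour route.
- **Other uses of the term.** Data entry includes a check that "serious adverse events have been reported and documented". Of the safety analysis, Safety evaluation and analysis says: "It is based mainly on the occurrence of adverse events and serious adverse events". Under Research ethics, a DSMB is to "periodically review the accumulated safety and efficacy data".

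**The concern.** The definition decides what reaches the study lead and the ethics committee quickly. It has no criterion for a life-threatening event, for an admission or prolonged stay shorter than 2 months, for reoperation, for lasting disability, or for death from a cause other than surgical complications.

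This matters for the comparison being made. The high-ligation arm adds mobilisation of the vein up to the pancreas and dissection of the root lymph nodes. If that extra dissection causes serious but survivable harm, the expedited route is where it should show first, and this definition keeps such events out unless the stay is very long. The same definition sets the SAE counts in the safety analysis, so those counts would leave out the same events.

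**Working it through.** No arithmetic is needed beyond one conversion; the check is a comparison of the rules.

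**Step 1. Compare the two thresholds.**

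| Feature of the event | Study endpoints (to be reported) | Definitions of adverse events (SAE) |
|---|---|---|
| Hospital stay | any admission or prolongation | at least 2 months |
| Death | any | only if due to surgical complications |
| Additional surgical or medical treatment | included | absent |
| Life-threatening event | not named | not named |
| Lasting disability | not named | not named |
| Deadline | none given | 24 h from discovery (SAE reporting) |
| Recipient | none given | study lead, then ethics committee |

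The thresholds differ on stay, death and treatment, and only the narrower one carries a deadline and a recipient.

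**Step 2. Run cases through the SAE definition as written.**

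- Anastomotic leakage with reoperation, survived, stay under 2 months: neither criterion is met, so there is no 24-hour report.
- Postoperative abdominal haemorrhage with reoperation, survived, stay under 2 months: same result.
- Cerebrovascular event, survived, stay under 2 months: same result. With a stay of 2 months or more, or with death judged a surgical complication, it does qualify.
- Death judged not to be due to surgical complications: not an SAE unless the stay criterion was already met.

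The first three are types of event on the protocol's own 30-day morbidity list.

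**Step 3. Look at timing.** The clock starts at discovery of the SAE. An event that qualifies only by length of stay cannot be confirmed as an SAE until about 2 months have passed, roughly 2 × 30 = 60 days. That is twice the 30-day morbidity window. For such events a 24-hour deadline no longer gives early warning.

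**Step 4. See whether another rule closes the gap.** The severity grades carry no reporting deadline. The Study endpoints rule has neither deadline nor recipient. DSMB review is periodic. None of them supplies an expedited report for the cases in Step 2.

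**Step 5. See what can be quantified.** The share of serious events missed would need complication rates, case fatality and the distribution of length of stay. The document gives none of these, so no share is computed.

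**The case against.** The strongest reply is that the plan has two tiers that can work together. The Study endpoints section does not define SAEs; it sets a broad group to be reported, and the later sections single out a narrow group for fast handling. On that reading there is no strict contradiction. This largely stands. What remains is that the fast tier is too narrow and that its relation to the broad tier is not stated, so a site cannot tell from the text how quickly, or to whom, an event in the broad group must be reported.

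Four stronger readings may tempt a reader, and the document does not support them.

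- *Most serious complications are missed, or SAE counts will be close to deaths alone.* There are no rates or lengths of stay from which to judge this.
- *The DSMB will not see these events.* Its remit is the accumulated safety and efficacy data and is not limited to SAEs; it may also recommend early termination on safety grounds.
- *A harm signal would go unnoticed.* Leakage, haemorrhage, intra-abdominal infection, obstruction, cardiovascular and cerebrovascular events and mortality are secondary endpoints whatever their SAE label, and the safety analysis uses all adverse events as well as SAEs.
- *SAE rates cannot be compared between the arms.* The same definition applies to both, so they can be compared. They would simply describe a narrow class of events.

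It may also be said that an article condenses a longer protocol. That excuses missing detail, but here a complete definition is stated and is itself too narrow.

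**Conclusion.** The point holds as a defect in expedited safety oversight and in what the SAE counts represent. If the plan is followed as written, every complication survived with a stay under 2 months, however dangerous, falls outside the 24-hour report, the ethics committee assessment and the suspension step. So does a death attributed to another cause, unless the stay criterion was already met. Events that qualify by stay alone arrive about 2 months late.

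The primary endpoint and the 30-day morbidity comparison are not affected, and the events are still recorded, reported in some form and open to periodic DSMB review. The conclusion rests on reading the two SAE criteria as a complete list, which is how the sentence is written, and on the expedited route applying to SAEs alone, which is how SAE reporting is written. How many events are affected cannot be determined from the document.

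**What to change.** Reconcile Study endpoints, Definitions of adverse events and SAE reporting into one SAE definition:

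1. Remove the 2-month threshold, and count admission or prolonged stay of any length.
2. Remove the limit on cause of death, and count death from any cause.
3. Add life-threatening events and lasting disability. Both would be new; neither appears in the Study endpoints list.
4. State which additional surgical or medical treatments qualify. If every treatment counted, minor measures for events such as incision-site or urinary infection could flood the 24-hour route.
5. Apply the 24-hour pathway, the data-management check and the SAE tables in the safety analysis to this definition.

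The cost is more expedited reports to process and a notification to the sites and their ethics committees. If recruitment has begun, which the document does not state, earlier events must be reclassified so that SAE counts are consistent throughout. Little new data collection should be needed, because the protocol already requires all adverse events to be recorded and the broader group to be reported.

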#### SAE reporting

When an SAE occurs, reasonable medical measures must be taken immediately. The physician or research assistant who has confirmed the SAE should report to the research director of the participating institution; the person in charge of the research unit or the acting person in charge of the research unit shall report the SAE to the person in charge of the study within 24 h of the discovery of the SAE, the person in charge of the study shall report the SAE to the ethics committee of the unit, and the ethics committee of the unit shall fully assess the urgency, importance, and impact of the SAE. After evaluation and discussion, the study may be suspended if necessary.

### Quality-control measures

#### Participation in the center screening

It should be ensured that the surgical team of each center has the ability to carry out standardized laparoscopic radical rectal cancer surgery and has performed >50 laparoscopic rectal cancer resections (≥30 procedures annually). We have standardized procedural videos and images available for the participating centers.

#### Enrollment

All the enrolled patients should be screened in strict accordance with the inclusion criteria and the qualified research centers can conduct intraoperative randomization after intraoperative exploration and definitive radical surgical resection to minimize the rejection rate of the enrolled patients.

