#### Randomization

After the test is completed, the researcher logs in to the data access service (DAS) for the interactive web response system (IWRS) to apply for a random number and prints or downloads the randomization information of the DAS for the IWRS for storage. The stochastic flow chart is presented in Fig. 1.

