### Subject management

#### Subject exclusion criteria

After being selected for randomization, the patient requested to withdraw from the study because of various considerations.There are no data after entering the queue.Intraoperative findings of tumor involvement requiring multivisceral resection, distant metastasis, or inability to complete the planned laparoscopic radical resection.Other reasons need to be excluded as determined by the investigator.

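### The protocol fixes no single randomisation point and conflicts on whether randomised patients excluded for intraoperative findings or an uncompleted resection stay in the primary analysis.

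*Protocol article*

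**What the plan says.** Timing of allocation is described in two places.

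- Quality-control measures, Enrollment: qualified centres can conduct "intraoperative randomization after intraoperative exploration and definitive radical surgical resection", with the stated aim of keeping rejections of enrolled patients low.
- Random and blinding, Randomization: "After the test is completed, the researcher logs in to the data access service" to obtain a random number. The test is not named, and nothing links this step to the operation.

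Exclusion is described under Subject management, Subject exclusion criteria, a list separate from the eligibility criteria in Subjects of the study. Three of its items matter here:

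- "After being selected for randomization, the patient requested to withdraw from the study because of various considerations"
- "Intraoperative findings of tumor involvement requiring multivisceral resection, distant metastasis, or inability to complete the planned laparoscopic radical resection"
- "Other reasons need to be excluded as determined by the investigator"

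Retention is described in two places.

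- Dropout treatment says the data of withdrawn cases are kept and are needed for the full analysis set.
- Evaluation and analysis of efficacy promises an intention-to-treat analysis on the whole population and places patients whose assigned operation was changed in that population. It also forms the full analysis set by a minimal and reasonable culling of randomised subjects.

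The Blinding section states that surgeons know the allocated ligation level.

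**The concern.** A randomised comparison is protected when eligibility is settled before allocation and everyone allocated is analysed. Here neither is secured. If some centres allocate before exploration and others after it, the same finding at laparoscopy is a screening failure at one centre and a post-randomisation exclusion at another.

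The more serious item is failure to complete the planned resection, because it can occur after allocation under any workable timing. The high-ligation arm carries out the low-ligation steps and then adds mobilisation of the IMV to the pancreatic border and dissection of the root nodes (Major surgical steps, Step V). The rate of failure could therefore differ between arms. It is judged by surgeons who know the arm, and the list also has an open-ended discretionary item. If patients excluded this way have a worse prognosis, the arm that loses more of them looks better on DFS.

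**Working it through.** **1. Do the passages agree on timing?**

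- The IMV is ligated in Step II, before the rectum is separated (Step III) and the bowel removed (Step IV). Allocation after a completed resection would be too late to direct the randomised step, so the literal wording cannot be carried out.
- If allocation always followed an exploration that confirmed resectability, few randomised patients could later be excluded for metastasis or multivisceral involvement. The exclusion list nevertheless contains these findings beside an explicitly post-randomisation item.
- Research ethics requires consent before randomisation but does not fix when randomisation happens. No passage sets one time point.

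**2. Do the passages agree on who is analysed?**

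- A randomised patient who asks to withdraw is excluded under Subject exclusion criteria. The same patient is a dropout under Shedding criteria, with data kept for the full analysis set under Dropout treatment.
- A patient whose planned resection fails is excluded under Subject exclusion criteria. The same patient arguably belongs to the intention-to-treat population as someone whose assigned operation changed, yet could still be culled from the full analysis set.

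**3. How large could the effect be?**

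The protocol gives no figure on this point. The stated 758 per group is used only as the arm size. It is roughly reproduced as follows. The planned hazard ratio is ln(0.85)/ln(0.78) = 0.654. Events needed = 4 × (1.960 + 0.842)² / [ln(0.654/0.90)]² = 308. Treating the 20% loss as a dropout hazard over 3 years (an assumption) gives 746 to 772 per group.

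Assumed inputs, none from the documents: no true effect; a fraction e = 5–10% excluded from one arm and none from the other; hazard h = 1.5–2.5 times that of patients kept. The whole-arm 3-year DFS of 78% is the control-group planning figure.

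DFS s among patients kept solves (1 − e)s + e·s^h = 0.78.

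- e = 5%, h = 1.5: s = 0.7845 (0.95 × 0.7845 + 0.05 × 0.7845^1.5 = 0.780). The gain is 0.45 points, and the apparent hazard ratio is ln(0.7845)/ln(0.78) = 0.977.
- e = 10%, h = 2.5: s = 0.8026 (0.90 × 0.8026 + 0.10 × 0.8026^2.5 = 0.780). The gain is 2.26 points, and the apparent hazard ratio is 0.885.

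Expected events use 2 years of uniform accrual plus 3 years of follow-up, ignoring dropout. The event probability is 1 − (e^(−3λ) − e^(−5λ))/(2λ), where this e is the exponential constant and λ = −ln(DFS)/3. At 78% this is 0.281, so the intact arm has 758 × 0.281 = 213 events. The depleted arm has 199 (mild case) or 173 (severe case).

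False-positive rate = P(Z > 1.96 − shift), where shift = −ln(HR/HR₀)/√(1/d₁ + 1/d₂) and HR₀ is the null value tested.

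| Case | Standard error | Against HR₀ = 1 | Against HR₀ = 0.90 |
|---|---|---|---|
| Mild | √(1/199 + 1/213) = 0.099 | about 4.2% | about 0.3% |
| Severe | √(1/173 + 1/213) = 0.102 | about 22% | about 3.6% |

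With only the 308 planned events (standard error 2/√308 = 0.114), the ranges are about 4–19% and 0.4–3.5%. The nominal one-sided rate is 2.5%.

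**4. Scale.** If 3–10% of all 1,516 were excluded (again assumed), 45 to 152 patients would leave after allocation.

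**The case against.** **After resection.** A reader might infer that centres are meant to allocate once the specimen is out. The text does not support that. The stated purpose is to reduce the rejection of enrolled patients, which makes sense only if radical resection has been confirmed as feasible before allocation. This is a wording fault.

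**Early allocation.** A reader might also infer that the exclusion list proves allocation before exploration. It does not. The intraoperative item does not itself mention randomised patients; that is inferred from the first item on the list and from its place under Subject management. Metastasis and multivisceral findings could be pre-allocation findings, and exploration is common to both arms.

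**Retention.** The intention-to-treat statement and Dropout treatment do point towards keeping such patients. That mitigation is real but incomplete, since the same section allows culling and the exclusion list says otherwise.

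**Size.** One-arm exclusion of 5–10% is a worst case with no support in the documents. Only failures in the added high-ligation step, or unblinded discretion, could differ by arm. The sample-size section also sets a superiority margin of 0.90, against which the rate barely exceeds the nominal level even in the severe case. However, Statistical analysis names only a log-rank test at P < 0.05, so a test against 1 remains open.

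**DFS origin.** The protocol counts DFS from surgery and does not argue that this coincides with randomisation. Nothing here rests on that.

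The permissive wording, the undefined test, and exclusion for a resection that fails after a known allocation all stand.

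**Conclusion.** The inconsistency is real and should be fixed. The protocol sets no single allocation point, and its rules on exclusion and retention cannot both be applied to the same randomised patient. Where allocation precedes exploration, or the planned resection fails afterwards, patients can be removed for reasons that may depend on the arm.

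The size is unknown because no exclusion rate is given. The 0.4–2.3 point gain and the 4–22% false-positive rate are illustrative upper-end figures. They hold only if one arm loses 5–10%, the other loses none, those lost have 1.5–2.5 times the hazard, and the test is against a hazard ratio of 1. Against the 0.90 margin the rate stays below about 4%, and balanced exclusions would largely cancel. A reader might take the 22% as the expected bias of the trial; the documents do not support that.

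**What to change.** - In Randomization and in Quality-control measures, Enrollment, state one rule: every centre must request allocation in the IWRS after exploration has confirmed eligibility and resectability, and before IMV ligation.
- Replace the phrase that makes resection the trigger with confirmation that radical resection is feasible, and remove or define the unnamed test.
- In Subject exclusion criteria, make findings at exploration pre-randomisation screening failures.
- In Evaluation and analysis of efficacy, state that every randomised patient, including those whose planned resection is not completed, stays in the primary intention-to-treat analysis. Reconcile the withdrawal and discretionary exclusion items and the culling clause with that rule.

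The cost is protocol wording and a memo to sites. The IWRS is already in use and intraoperative allocation is already intended. The one practical burden is web access in theatre.
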